## Abstract

**Background:**

Overweight is considered an important risk factor for diseases in the context of metabolic syndrome. Lifestyle modifications are the means of choice to reduce weight in persons with a Body Mass Index of 28 to 35. The study examines whether there are any differences between two intervention strategies regarding weight reduction in overweight persons.

**Methods/Design:**

The study is a multicentre randomized controlled trial with observation duration of 12 months. Eight study centres are involved to include a minimal sample size of 150 participants. Randomization ratio is 2:1. Feasible persons are checked according to inclusion and exclusion criteria and after given informed consent are assigned randomly to one of two intervention programs: A) intervention group: comprehensive lifestyle modification program (Individual Health Management IHM) with 3 months reduction phase plus 9 months maintaining phase, B) control group: written information with advice for healthy food habits (Usual care UC). Participants of the IHM group have access to a web-based health portal and join 3 full-day and 10 two-hour training sessions during the first 3 months. During the remaining 9 months four refresh trainings will be performed. There are 3 different diet strategies (fasting, two-day diet, meal replacement) for free choice. Participants of the control group are provided with acknowledged rules for healthy food according to the German Nutrition Society (DGE). Examinations are conducted at baseline, after 3, 6, 9 and 12 months. They include body weight, waist circumference, blood pressure, laboratory findings and a bio-impedance analysis to measure body composition. Statistical analysis of the primary outcome ‘change of body weight after 12 months’ is based on ITT population including analysis of variance of the weight differences between month 0 and 12 with the factors ‘group’, ‘baseline value’ and ‘study centre’. Secondary outcomes will be analyzed exploratively.

**Discussion:**

The monitoring of the study will implement different measures to enhance compliance, avoid attrition and ensure data quality. Based on a blended learning concept and using web-based e-health tools the program promises to achieve sustainable effects in weight reduction.

**Trial registration:**

German Clinical Trials Register Freiburg (DRKS): DRKS00006736 (date registered 20/09/2014).

**Electronic supplementary material:**

The online version of this article (doi:10.1186/s40608-015-0069-x) contains supplementary material, which is available to authorized users.

## Background

There is an increasing trend for overweight and obesity worldwide. In 2008, 35 % of adults aged 20+ were overweight (BMI ≥ 25 kg/m^2^). The worldwide prevalence of obesity has nearly doubled between 1980 and 2008 [1]. In a more recent analysis this trend has been confirmed [2]. In developed countries like US the figures are markedly higher. Approximately two thirds of adults are overweight (BMI of 25-29.9) or obese (BMI ≥ 30) [3]. The German Health Interview and Examination Survey for Adults (DEGS1), conducted from 2008 through 2011, provides current data about overweight and obesity among adults in Germany based on a representative sample of 7116 persons [4]. Prevalence of overweight defined as BMI ≥ 25 is 53 % for females and 67 % for males with increasing rates in higher age groups. While prevalence of obesity grade I (BMI 30-35) is similar in both sexes (16 % in women, 18 % in men) pre-adipositas (BMI 25–30) is more frequent in men (44 %) than in women (29 %).

Obesity is associated with many comorbid conditions which has major implications for longevity, quality of life and healthcare costs [5]. It could be shown that a strong and linear association exists between Body-Mass-Index (BMI > 20) and the risk of developing type 2 diabetes, hypertension, CVD, and other chronic diseases in both men and women [6].

Therapeutic interventions aiming at weight reduction range from multiple modalities including behavioural therapy and pharmacotherapy integrating clinical and community approaches [7] to lifestyle counselling and mere nutritional programs. Enhanced lifestyle counselling proved to be superior to usual care with respect to weight reduction [8]. Compared to minimal or no intervention it could be shown that self-management plus exercise prevented weight increase in patients with cardiometabolic disease [9]. A systematic review comparing the effects of different popular diets revealed that only weight-watchers program was beneficial to usual care in RCTs of 12 month duration [10].

From the findings in the literature one has to conclude that a sustainably successful treatment of overweight requires intensive education, counselling, multiple resources, and ongoing support. The Individual Health Management (IHM) is a program which meets these prerequisites. It is theory driven and designed to promote changes across multiple health behaviours simultaneously aiming for participation of healthy and ill people to enhance their individual responsibility, self-determination and health literacy [11]. Self-management supporting the participants to optimize physiological skills and psycho-social competencies is considered the core element of the intervention. It comprises areas like physical activity, nutrition, self-efficacy and social support. To enhance sustainability they are to be trained and implemented into daily activities. The lifestyle program combines a web-based lifestyle modification program, physician-led counselling via face-to-face or telemedicine visits and various forms of group sessions to achieve behavioural change (blended learning concept). To ensure a high standard of professional service, IHM health staff graduates in a 200 h theoretical and practical training in comprehensive life style medicine.

Although the basic concept of IHM is very broad and multifaceted the planned study will focus on weight reduction as target parameter. Due to a comprehensive change in lifestyle the effects are expected to be enduring. Thus, the decisive measurement of body weight should be one year after onset of the program. For weight monitoring in overweight persons including obesity grade I it is highly relevant to compare the effects of IHM with the common brief diet and lifestyle counselling used in daily routine of general practitioners. This is in line with the findings of a systematic review of RCTs on multifactorial lifestyle interventions in primary and secondary prevention [12].

The study is part of a comprehensive network program to install and maintain prevention programs for different risk groups at selected spas in Bavaria. The project is to contribute to the improvement of the medical quality of health services offered in the spas.

The primary objective of the study is to examine whether there are any differences between two intervention strategies (Individual Health Management versus usual care) regarding weight reduction at month 12 in overweight persons. Further objectives are the comparative analysis of secondary outcome parameters like Body-Mass-Index, waist circumference, laboratory findings, blood pressure and the ratio of fat, muscle mass and bodily water. Moreover, the descriptive comparison of both intervention groups include the analysis of the course of changes in body weight, a responder/non-responder analysis, and an analysis with respect to the applied dietary strategy.

## Methods/Design

### Study design

The study is a multicentre randomized controlled trial. The study duration for each participant is 12 months with five sequential examinations. It will be performed in total in 8 study centres located in different spa towns all over Bavaria, and complemented by the outpatient unit of the Competence Centre for Complementary Medicine and Naturopathy at Klinikum rechts der Isar, Munich. The centres in the spas are affiliated to private practices of General practitioners. These centres are committed to be a part of the local core teams promoting Individual Health Management (IHM) which are pooled into a centrally coordinated network of health promotion called ‘IHM-Campus’.

### Recruitment and participants

Measures for recruitment of feasible study participants include different strategies which are not regulated equally across all study centres. The methods consist of: search in the databases of the GP practices, conduct of local action days to attract population interested in overweight and prevention from diabetes, advertisements in local media with the offer for obese persons to participate in a clinical study. All interested persons will contact the local IHM teams which will provide basic information around the study and a tool to screen for the main inclusion criteria. All persons who apparently should comply with the requirements of the study are invited to a personal appointment with the trial physician to undergo a comprehensive examination of the criteria for inclusion and exclusion. Potential participants will be informed on background, objectives, benefit and risks of the study by a leaflet as well as orally by the trial physician.

### Inclusion/exclusion criteria

Persons of both sexes, aged 18 to 67 years, with moderate overweight defined as Body-Mass-Index from 28.0 to 35.0, can be included to the study. A written informed consent is mandatory.

Persons will not be included if one of the following exclusion criteria are present: not legally competent, insufficient skills in German language, no private access to internet, already known pregnancy, known psychiatric disease including eating disorder or addiction, known diseases of the eyes, known diabetes type 1 or 2, hypertension grade II (systolic BP ≥ 160 mmHg or diastolic BP ≥ 100 mmHg) with/without medication, known heart disease, known gastric or duodenal ulcers, diseases of the liver or kidneys which do not allow an increased intake of proteins, disease-related impairments hampering certain elements of the lifestyle program or therapeutic conditions not compatible with lifestyle modifications.

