### Interventions

The study compares two intervention arms (IHM = Individual Health Management; UC = Usual Care):*Group IHM*: Lifestyle program ‘Individual Health Management’ with an overall duration of 12 months is composed of 2 phases: i) the first 3 months (reduction phase) include 3 full-day so called’introduction days’ plus 10 two-hour weekly training sessions; ii) during the following 9 months (maintaining phase) participants are practicing lifestyle modifications by oneself supported by 4 full-day refresh training sessions. The program encompasses access to a web-based health portal (https://www.viterio.de/) providing detailed advice and instructions with respect to food, exercise and relaxation. Furthermore, this tool allows a personalized feed-back control of the progress made so far. IHM is implemented as a group intervention program with a group size of roughly 12. All training sessions will be performed in the local study centres. Details of the intervention concept and realization are described elsewhere [11]. All participants will be offered three different diet strategies: i) fasting (per week one regular day, five waiver days, one food restriction day with < 900 kcal plus fasting during week 7), ii) two-day diet (five regular days, two serial food restriction days with < 600 kcal), iii) meal replacement (one regular day, five waiver days, one food restriction day with meal replacement < 900 kcal plus meal replacement in week 7) for free choice.*Group UC*: This intervention is an active control intervention reflecting the common practice in usual care. Participants are provided with a leaflet containing 10 acknowledged rules for healthy food and physical exercise according to the German Nutrition Society (DGE). They will neither join the group sessions nor will get access to the web-based health portal.

Figure 1 shows the basic design of the study with the two treatment arms and all examinations.

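### The only reproductive exclusion is pregnancy already known, so an otherwise eligible breastfeeding woman can be randomised to IHM, where every diet includes days below 600 or 900 kcal

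*Protocol article*

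**What the plan says.** The Protocol article admits "Persons of both sexes, aged 18 to 67 years" with a BMI of 28 to 35, so women of childbearing age are in the target population. The exclusions are given as a list to be applied item by item: "Persons will not be included if one of the following exclusion criteria are present". The only item on reproductive status lies in "no private access to internet, already known pregnancy, known psychiatric disease including eating disorder or addiction". The list also screens for unsuitability of the diet in one respect, "diseases of the liver or kidneys which do not allow an increased intake of proteins", and ends with a general clause: "disease-related impairments hampering certain elements of the lifestyle program or therapeutic conditions not compatible with lifestyle modifications".

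Under Interventions, IHM participants choose among three diets. The fasting option has "one food restriction day with < 900 kcal plus fasting during week 7". The second option is the "two-day diet (five regular days, two serial food restriction days with < 600 kcal". The meal replacement option has "one food restriction day with meal replacement < 900 kcal plus meal replacement in week 7". Randomisation sets the ratio at 2 for IHM to 1 for usual care. Table 1 places the eligibility check at month 0 only and schedules no pregnancy test.

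**The concern.** The authors considered reproductive status and the suitability of the diet when they wrote the list, but the reproductive item stops at a pregnancy known at inclusion. Breastfeeding can be present at enrolment and can coincide with the restricted days, yet it is not on the list. A centre that applies the criteria exactly would enrol such a woman and might assign her to a programme built around fasting or low-calorie days.

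What is at stake is the safety of participants and, for a breastfeeding woman, of her infant. The statistical result is not the issue: any effect on the precision of the 12-month weight change cannot be quantified from the article and is not used as support.

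**Working it through.** No figure of the plan is disputed, so the check is mainly a reading of the criteria against the interventions, with a little arithmetic.

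**1. Does any criterion reach breastfeeding?**
- Reproductive item: pregnancy only, and only if already known.
- Liver and kidney item: does not apply.
- General clause: it has two limbs, impairments that are disease-related and conditions that are therapeutic. Breastfeeding is neither a disease nor a therapy, so the wording does not cover it.
- The remaining items (legal competence, language, internet access, psychiatric and eye disease, diabetes, hypertension, heart disease, ulcers) do not apply.

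An otherwise eligible breastfeeding woman therefore meets every written criterion.

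**2. Chance of assignment to IHM.** From the 2:1 ratio under Randomisation: 2/(2+1) = 0.667, or 67%. The group sizes under Statistical analysis agree: 98/(98+49) = 98/147 = 0.667.

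**3. Does free choice of diet offer a way round?** The days listed for each option add up to one week (1+5+1, 5+2 and 1+5+1 = 7), so each is read as a weekly pattern.

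| Option | Restricted days per week | Week 7 |
|---|---|---|
| i, fasting | 1 day below 900 kcal | fasting |
| ii, two-day diet | 2 consecutive days below 600 kcal | nothing added |
| iii, meal replacement | 1 day below 900 kcal | meal replacement |

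No option has zero restricted days. The article describes no modified diet for breastfeeding women.

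**4. How many restricted days?** The article does not say for how many weeks, *w*, the pattern runs, so a count needs an assumption. Options i and iii give *w* − 1 days outside week 7; option ii gives 2*w* days. Two assumptions are shown: 10 weeks, matching the 10 weekly training sessions, and 12 to 13 weeks, the length of a 3-month reduction phase.

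| Assumed *w* | Options i and iii, outside week 7 | Option ii |
|---|---|---|
| 10 | 9 | 20 |
| 12 | 11 | 24 |
| 13 | 12 | 26 |

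These counts only illustrate the range. The point rests on step 3, that the number is not zero under any option.

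**The case against.** The strongest objection is that this is a journal article, and the full protocol or a screening form may carry further wording. That would be decisive if the article were silent on reproductive status. It is not: it states the criterion, in narrow terms, within a list detailed enough to give blood pressure limits. What stands is that the article cannot show what was done at the centres. A reader might infer that breastfeeding women were enrolled, or that no other document excludes them. The article supports neither.

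Second, no section says that these diets are unsafe in breastfeeding, and no figure for harm is given. That is so, and none is claimed here. The point is that the list screens for pregnancy and for one dietary contraindication, and leaves this closely related state unscreened.

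Third, there are other safeguards: a personal appointment with the trial physician, information on risks, written consent, physician-led counselling within the programme, adverse-event recording from month 3 and ethics approval. These help, but none is an eligibility criterion, and adverse-event recording acts only after exposure.

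Fourth, a reader might infer that assignment to IHM compels a woman to follow the restricted days. The documents do not support that. Interventions describes the diets as offered, and the Discussion (Quality assurance and bias) says that varied individual practice does not automatically lead to exclusion. She could leave out restricted days, but the plan does not direct her to.

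Fifth, a reader might give planned conception the same weight. The article gives no ground for that: such a pregnancy may begin after the 3-month reduction phase, the intention is self-reported and cannot be verified, and asking about it does not prevent unplanned pregnancy.

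**Conclusion.** The concern holds for breastfeeding. Followed as written, the exclusion list lets an otherwise eligible breastfeeding woman be enrolled, with a 67% chance of IHM, where every diet offered contains days below 600 or 900 kcal. This is a stated criterion drawn too narrowly. It is a minor, inexpensive safety correction.

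The conclusion assumes that centres apply the list by its wording and that no unseen document adds a breastfeeding exclusion. Neither the number of women affected nor the exact number of restricted days can be derived from the article. No bias or loss of power in the primary analysis is claimed.

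**What to change.** In the exclusion list, replace the present pregnancy item with: *known pregnancy or current breastfeeding*. The trial physician asks this at the screening appointment already described under Recruitment and participants. If the full protocol already says so, the article only needs to be brought into line with it.

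Optionally, add *pregnancy planned within the next 12 months*, as a secondary item with the limits noted above.

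The cost is one question, or two with the optional item, a few more exclusions and a slightly narrower population. No visit, procedure, sample size or analysis changes.

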### Randomisation

Eligible participants will be randomized immediately after formal inclusion to the study. The trial physician will open the closed envelopes in strictly sequential order of the enrollments and the allocated treatment arm will be disclosed to the study participant. The allocation ratio is 2:1, means 2 for IHM group and 1 for the comparison group. Randomisation and allocation envelopes will be prepared by an independent data manager at the institute for medical statistics and epidemiology at TU Munich.

### Interventions

The study compares two intervention arms (IHM = Individual Health Management; UC = Usual Care):*Group IHM*: Lifestyle program ‘Individual Health Management’ with an overall duration of 12 months is composed of 2 phases: i) the first 3 months (reduction phase) include 3 full-day so called’introduction days’ plus 10 two-hour weekly training sessions; ii) during the following 9 months (maintaining phase) participants are practicing lifestyle modifications by oneself supported by 4 full-day refresh training sessions. The program encompasses access to a web-based health portal (https://www.viterio.de/) providing detailed advice and instructions with respect to food, exercise and relaxation. Furthermore, this tool allows a personalized feed-back control of the progress made so far. IHM is implemented as a group intervention program with a group size of roughly 12. All training sessions will be performed in the local study centres. Details of the intervention concept and realization are described elsewhere [11]. All participants will be offered three different diet strategies: i) fasting (per week one regular day, five waiver days, one food restriction day with < 900 kcal plus fasting during week 7), ii) two-day diet (five regular days, two serial food restriction days with < 600 kcal), iii) meal replacement (one regular day, five waiver days, one food restriction day with meal replacement < 900 kcal plus meal replacement in week 7) for free choice.*Group UC*: This intervention is an active control intervention reflecting the common practice in usual care. Participants are provided with a leaflet containing 10 acknowledged rules for healthy food and physical exercise according to the German Nutrition Society (DGE). They will neither join the group sessions nor will get access to the web-based health portal.

Figure 1 shows the basic design of the study with the two treatment arms and all examinations.

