### Statistical analysis

Based on indications from the literature we assumed a mean reduction for body weight after 12 months of 6 kg under IHM and of 3 kg under usual care conditions. Given a common standard deviation of 6 kg for the change in weight the sample size for the *t*-test for independent groups (α = 0.05, 2-sided, power 80 %) is estimated as 98 in one group and 49 in the second (allocation ratio 2:1). Hence, the total sample size is 150 participants.

The confirmatory analysis will be conducted using a 2-sided significance test at the 5 % significance level. Based on the intent-to-treat population the primary outcome (change in body weight Δ_month 0 – month 12_) will be tested by analysis of variance with the grouping factor ‘intervention’ controlled for baseline value. The factor ‘study centre’ will also be included to the test model. In participants with missing data for weight at month 12 (drop-outs) an adequate conservative imputation technique will be applied.

Secondary endpoints will be analyzed analogously but using an explanatory approach. Hence, a correction of the error probabilities due to multiple testing is not indicated. These analyses will be performed on both intent-to-treat and per-protocol populations. A responder analysis with respect to the primary outcome will be performed using a responder definition with a threshold of 7.5 % weight reduction at month 12 compared to the baseline value. Depending from the number of participants who chose the different nutritional regimen a subgroup analysis within the IHM group will be performed.

All captured data will be analyzed descriptively by appropriate statistical parameters: absolute and relative frequencies for categorical data and arithmetic means, medians, standard deviations for numerical data. Where indicated, 95 % confidence intervals will be presented.

Apart from the confirmatory analysis a series of sensitivity analyses will be performed to explore the impact of different factors on the results of the analyses. Relevant factors are among others adherence to the protocol, adherence to the intervention program IHM and different responder definitions.

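### IHM is delivered in training groups of about 12, but the sample size and primary model treat IHM participants as independent; if outcomes correlate within groups, the standard error is too small and power is overstated.

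*Protocol article*

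**What the plan says.** Under Interventions, the protocol article says that "IHM is implemented as a group intervention program with a group size of roughly 12". IHM participants attend three full days and ten two-hour sessions in the first three months, then four refresher days, all at the local centre. UC participants get a leaflet, join no sessions and have no access to the web portal.

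Under Statistical analysis, the trial is sized with a t-test "for independent groups (α = 0.05, 2-sided, power 80" per cent). The assumptions are a "mean reduction for body weight after 12 months of 6 kg under IHM and of 3 kg under usual care conditions". The spread is fixed by "Given a common standard deviation of 6 kg for the change in weight", and the result "is estimated as 98 in one group and 49 in the second (allocation ratio 2:1"), rounded to 150 in total.

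The same section fixes the primary test: "The confirmatory analysis will be conducted using a 2-sided significance test at the 5 % significance level", using an analysis of variance with intervention and baseline value. It adds that "The factor ‘study centre’ will also be included to the test model". It gives no ICC, design effect, training-group term or cluster-robust variance, and no other section mentions correlation within training groups.

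**The concern.** Members of one training group share sessions and peers for a year. If that makes their weight changes more alike, about 100 IHM participants carry less information than 100 independent people. UC participants have no such shared delivery, so the correlation arises in one arm only.

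A standard error that ignores this is too small. The confidence interval for the treatment difference would be too narrow, the single confirmatory test could reject too often, and the planned power would not be reached. The article itself names the test, the model factors and the sample-size method. This is therefore a stated choice, and an analysis plan that followed it would carry the problem forward.

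**Working it through.** **Inputs from the protocol article.** Difference 6 − 3 = 3 kg; SD 6 kg; two-sided α 0.05; power 80%; allocation 2:1; total 150, hence 100 IHM and 50 UC; group size about 12; 8 centres.

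**Assumptions.** The ICC is not given, so 0.01 to 0.10 is used. 100/12 ≈ 8 groups, which for 8 centres suggests about one group per centre; this layout is inferred.

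**1. The plan's own figure.** For independent participants, n(UC) = (1.96 + 0.8416)² × (36/9) × (1 + 1/2) = 47.1. Rounded up, that is 48 UC and 96 IHM, 144 in total. Exact t-test power is 80.2% at 96 + 48 and 81.0% at 98 + 49. The stated 98 and 49 are reproduced closely enough, under independence.

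**2. Clustering in the IHM arm only.**

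- Design effect: DE = 1 + (12 − 1) × ICC
- SE ignoring groups: 6 × √(1/100 + 1/50) = 1.039 kg
- SE allowing for groups: 6 × √(DE/100 + 1/50)
- Actual α of the unadjusted test: 2 × [1 − Φ(1.96 × 1.039/SE)]
- Power with the correct SE: Φ(3/SE − 1.96)
- UC participants for 80% power: (1.96 + 0.8416)² × (36/9) × (1 + DE/2), rounded up, with twice as many IHM

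Example at ICC 0.05: DE = 1.55; SE = 6 × √(0.0155 + 0.02) = 1.130 kg; power = Φ(2.654 − 1.96) = 75.6%; n(UC) = 31.4 × 1.775 = 55.7, so 56 + 112 = 168.

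| ICC | DE | SE (kg) | Actual α | Power, 100 + 50 | Total for 80% power |
|---|---|---|---|---|---|
| 0 | 1.00 | 1.039 | 5.0% | 82.3% | 144 |
| 0.01 | 1.11 | 1.058 | 5.4% | 80.9% | 147 |
| 0.02 | 1.22 | 1.077 | 5.9% | 79.6% | 153 |
| 0.05 | 1.55 | 1.130 | 7.2% | 75.6% | 168 |
| 0.10 | 2.10 | 1.215 | 9.4% | 69.5% | 195 |

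Totals are before drop-out.

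**3. Does the centre term help?** The planned model (arm, baseline, fixed centre) was simulated with no average treatment difference and 15,000 replicates per setting. The first layout has 8 centres, each with one IHM group of 12 and 6 UC participants. The second has 4 centres with two IHM groups each.

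| ICC | One group per centre | Two groups per centre |
|---|---|---|
| 0 | 5.1% | 4.8% |
| 0.01 | 5.4% | 5.6% |
| 0.02 | 5.7% | 5.9% |
| 0.05 | 7.4% | 7.7% |
| 0.10 | 10.3% | 9.8% |

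A separate simulation of the first layout gave 5.2%, 5.5%, 5.9%, 7.1% and 10.0%. The centre term does not remove the excess. A centre main effect shifts both arms equally, while a training-group effect shifts only the IHM participants. With one group per centre it acts as a centre-by-treatment effect, which the model omits.

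**4. Few groups.** The power figures above use the normal approximation. A conservative centre-level test with 7 degrees of freedom had about 60% power at ICC 0.05. A mixed model with small-sample degrees of freedom should lie between that and 75.6%.

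**The case against.** **No correlation is documented.** A reader might infer that type I error does exceed 5%. The documents do not support that, because they give no ICC and the inflation exists only if the correlation is positive at month 12. At 0.01 the test is close to nominal and 147 participants suffice; at 0.02 power is 79.6% against a planned 80%. This stands, and the point must be conditional.

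**Randomisation is individual.** If IHM, group delivery included, changed nobody's weight relative to UC, delivery would create no group variance and the test would keep about 5%. The inflation applies when the average difference is zero but groups truly differ. This also stands for the test. It rescues neither the confidence interval nor the power when effects exist.

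**Contact is front-loaded.** After month 3 participants mostly practise alone, with a personal web portal and a diet of their own choice. That may dilute the correlation by month 12, but cannot rule it out.

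**Parts of the layout are inferred.** It is tempting to say that each group shares one coach and that each centre runs one group. The article says neither. It describes trained coaches at the centres, recruitment methods that vary between centres, and a Munich outpatient unit that complements the 8 centres. Smaller groups would lower the design effect. The argument needs only shared sessions, and the result was similar with two groups per centre.

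**Study centre is already in the model.** This looks like an adjustment, but the simulation shows that it is not one.

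**Conclusion.** The point holds in conditional form. The article describes one-arm group delivery, and its sample size and primary model ignore it. If weight change is positively correlated within IHM groups, the standard error is understated and power overstated, and the centre term does not repair this.

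The direction is clear but the size is not. Over an assumed ICC of 0.01 to 0.10, type I error runs from about 5.5% to about 10%, and power with 100 and 50 participants from about 81% to 69.5%, before the few-groups penalty. The effect is negligible at the low end and material from about 0.05, a value the documents neither support nor exclude.

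A reader might go further and conclude that 150 participants are too few or that the primary test is invalid. Without an ICC, neither follows. The anticipated 10% attrition is a separate matter and is not in these figures. This should be fixed, because it bears on the only confirmatory test, but it is not a fatal flaw.

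**What to change.** 1. Record a training-group ID for every IHM participant. Without it, later adjustment may be impossible.
2. Make the primary analysis a mixed ANCOVA with fixed intervention, baseline weight and centre, plus a random training-group effect in the IHM arm only (UC participants as singletons), with Kenward-Roger or Satterthwaite degrees of freedom. Provided that each centre also has UC participants, the group variance can be estimated alongside the centre effects. Fix this before results are seen, so that the model is not chosen on them.
3. Restate power for 150 participants over an assumed ICC range of 0.01 to 0.10, allowing for the small number of groups.

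The cost is one extra variable and revised analysis wording. The confidence interval will be somewhat wider, the group variance will be imprecise with about eight groups, and the stated power will be lower. No extra participants are needed for the change itself, but it does not restore lost power: holding 80% would take 168 in total at ICC 0.05 and 195 at 0.10 by the normal approximation. Keeping 150 means accepting the lower figure openly.
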